### Sample size

R version 4.2.2 for Windows (R Foundation for Statistical Computing, Vienna, Austria) was used for the sample size calculation in a linear mixed-effect model (sjstats package). The R statistical computing environment will also be used for future model fitting and evaluation.

We used appropriate methods for two-level-designs [25] to determine sample size requirements for a cRCT with 3 experimental groups, 4 classrooms per experimental condition, 22 participants per cluster. For our linear mixed-effects model, a sample size of approximately 88 participants per experimental condition for a total sample size of 264 was sufficient to achieve 80% power to detect an effect size of Cohen’s *d* = 0.4 at an alpha level of 0.05. A medium effect size was assumed based on previous work on digital mental health literacy interventions [26].

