#### Statistical methods

Our study will consist of a multisite cluster randomized trial in which the unit of measurement is at student-level, while randomization takes place at the unit of assignment, at classroom-level. Consequently, it is a low bias cluster-level RCT with potential joiners (i.e., individuals not in intervention clusters at random assignment but who enter later) being excluded and scant possibility of “contamination” or “treatment spillover” to the control classrooms. Analyses will employ linear mixed model with individual-level repeated measures nested within classrooms, nested within schools. Adhering to WWC group design standards [42], the model will include indicators for each intervention period and interaction terms for assignment to the intervention group and the period associated with the intervention. We will also report on robust standard errors from our fitted models to adequately account for dependence within clusters.

Nevertheless, youth research, and especially youth mental health research, has unique challenges concerning data gathering. First, although we adhere to a strategic research design to reduce missing data, patterns of attrition relating to individual and cluster-level factors will be investigated, including links to social and health variables. Second, challenges in gathering parental consent after classroom-level assignment to experimental condition would yield higher number of leavers, which constitutes individual-level attrition [42]. If data is missing at random, our analytic choice will yield unbiased estimates of treatment effects [43]. If data is missing not at random, weighting and multiple imputation would be used. In line with WWC standards [42] for cluster-level assignment RCTs, we will employ regression imputation, maximum likelihood, or nonresponse weights to address missing values while providing evidence that the approach appropriately adjusts the standard errors for clustering.

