## Discussion

The current trial aims to test the effectiveness of a mental health literacy intervention for high school students, aimed at improving academic performance, as well as increasing well-being and decreasing symptomatology. The intervention will be delivered via two different formats: (1) an educational one, which will be fully automated, and (2) a blended one which will additionally allow contact with facilitators, and it will be contrasted against a waitlist condition. Testing mental health literacy interventions is paramount, as not much is known about their effectiveness on outcomes such as academic performance and symptomatology. Furthermore, since the goal of mental health literacy interventions is to fill in the gaps that other mental health interventions cannot, in terms of their reach and cost-effectiveness, it also becomes highly relevant to test various modes of implementing such interventions, including fully automated ones. Additionally, testing the effectiveness of such interventions in varied cultural and socioeconomic contexts is timely, as this has been previously recognized as a limitation of the literature [19].

This endeavor, however, is not without its caveats. Firstly, contrasting active interventions against a waitlist control group can artificially inflate effect sizes. However, this approach is more ecological and cost-effective. If results will favor the SCHOLARS intervention, future studies should contrast it against active control conditions or psychological placebos. Secondly, there may be limited adherence to the intervention by the participants (i.e., dropouts). To this end, we aim to monitor and maintain close and constant contact with the enrolled schools, as to minimize drop-out and the risk of non-adherence by participants.

To conclude, the current study has the potential of advancing the field of mental health literacy interventions for adolescents. The success of such interventions might represent an important avenue for preventively addressing the development of mental health concerns and their associated consequences such as decreased academic performance.

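### The remedy named for data missing not at random (weighting and multiple imputation) rests, as described, on missing at random, and observed data cannot show when to apply it

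*Protocol article*

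**What the plan says.** The Statistical methods section fixes the main model: "Analyses will employ linear mixed model with individual-level repeated measures nested within classrooms, nested within schools". It then sets out a two-branch rule for missing data. The first branch reads "If data is missing at random, our analytic choice will yield unbiased estimates of treatment effects". The second reads "If data is missing not at random, weighting and multiple imputation would be used". The next sentence cites an external design standard and adds that "we will employ regression imputation, maximum likelihood, or nonresponse weights to address missing values", with evidence to be given that standard errors allow for clustering.

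The only step described for judging the missingness is that "patterns of attrition relating to individual and cluster-level factors will be investigated, including links to social and health variables". One cause of loss is expected in advance: "challenges in gathering parental consent after classroom-level assignment to experimental condition would yield higher number of leavers". The Discussion also lists dropout as a limitation. The article mentions no shift parameter, selection model, pattern-mixture model, reference-based imputation or tipping point.

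**The concern.** The second branch presents weighting and multiple imputation as the answer where the mixed model is no longer unbiased. In the form described, they need the same kind of assumption as the mixed model: given the variables used, missingness does not depend on the unseen outcome. Moving to them when that assumption fails does not address the failure.

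The switch itself cannot be operated. Attrition can be related to observed factors, but whether it also depends on unobserved values cannot be read from the observed data. An analysis meant for missing not at random (MNAR) therefore has to be planned regardless of what the attrition tables show.

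This matters here because participants are not blinded, the comparator is a waitlist, and well-being and symptoms are among the primary outcomes. Loss related to both arm and current symptoms is plausible. A reader could take the sentence as protection that the described methods do not give.

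**Working it through.** The plan gives no figure for bias or attrition, so there is none to reproduce. The check has three parts.

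**1. The assumption behind each named method**

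- Likelihood-based mixed model: MAR given the observed outcomes and the model terms.
- Multiple imputation with no shift: MAR given the variables in the imputation model.
- Nonresponse weighting: response independent of the unseen outcome given the variables in the response model.

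The last two can use more variables than the mixed model does, which may make MAR more plausible. Neither contains a term for dependence on the unseen value itself.

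**2. Simulation of the switch**

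Taken from the article: "to detect an effect size of Cohen’s *d* = 0.4" (Sample size), used as the true effect. Assumed, and not in the article:

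- two arms, 2,000 subjects, 150 replicates, no clustering
- baseline–outcome correlation 0.6
- dropout at random in the control arm, about 21%
- dropout in the treated arm dependent on baseline (MAR case), or on the subject's own outcome with worse outcomes lost more often, logit slope −1 per SD (MNAR case)

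| Case | Missing, treated / control | Likelihood | Multiple imputation | Weighting |
|---|---|---|---|---|
| MAR | 25% / 21% | 0.401 | 0.402 | 0.402 |
| MNAR | 19% / 21% | 0.512 | 0.514 | 0.514 |

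Monte Carlo standard errors are 0.004 (MAR) and 0.003 (MNAR). Under MAR all three recover 0.40. Under MNAR all three are about 0.11 too high, so switching corrects nothing in this setting. All three used the same single baseline covariate, so their close agreement is built in. The simulation shows that the method alone does not help; it does not test the gain from auxiliary variables.

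**3. What governs the size**

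Let p be the fraction lost in an arm and δ the amount by which the lost students are worse than MAR predicts, in SD. A MAR analysis makes that arm look better by p × δ, so

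bias in the difference = p(active) × δ(active) − p(waitlist) × δ(waitlist).

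All inputs below are assumed:

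- Equal shift 0.5, loss 25% and 10%: 0.5 × (0.25 − 0.10) = 0.075 SD; 0.075 / 0.4 = 19%.
- Equal shift 0.5, loss 30% and 10%: 0.5 × (0.30 − 0.10) = 0.10 SD; 0.10 / 0.4 = 25%.
- Equal shift 0.5, equal loss 20%: 0.5 × 0 = 0.
- Shift 0.5 in the active arm only, equal loss 20%: 0.20 × 0.5 − 0.20 × 0 = 0.10 SD.

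The simulated MNAR case is of the last kind. A bias of 0.114 with 19.2% lost in the treated arm corresponds to δ = 0.114 / 0.192 = 0.59 SD in that arm. Similar attrition rates across arms are therefore no reassurance.

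**The case against.** The strongest reply is that the article names techniques, not their MAR versions. Multiple imputation can carry a shift and weights can carry a selection parameter, and the remedy proposed here is itself a form of multiple imputation. The values of such parameters are ordinary analysis-plan detail. It is true that the named technique is compatible with the fix and that missing values of a parameter would be no finding. But the article does more than stay silent. It assigns methods to the MNAR case with no sign of an MNAR component, and makes their use depend on a condition that the data cannot settle.

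A second reply also has force. The article plans to examine attrition against social and health variables, and its questionnaire battery is wide. Imputation or weights using those variables could remove bias that a mixed model with only period and assignment terms would keep. So it would be too strong to say that switching removes none of the bias. That holds only for the part that depends on unobserved outcomes given everything included.

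A reader might draw three further inferences that the text does not support:

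- That the main analysis will be chosen after attrition is seen. The linear mixed model is already fixed; the list joined by the word or concerns the handling of missing values, and maximum likelihood is how such a model usually handles missing outcomes.
- That single imputation is planned. The article says only regression imputation, and promises evidence on standard errors under clustering.
- That the article claims its results will be robust to MNAR. It makes no such statement.

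**Conclusion.** The point stands as a correction to one stated rule. As written, the MNAR branch gives no protection against dropout that depends on unobserved outcomes, and its trigger cannot be evaluated. Weighting and imputation with auxiliary variables remain useful, but as MAR analyses.

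No bias figure is established for this trial. The 0.075 to 0.10 SD range rests wholly on an assumed shift of 0.5 SD, equal in both arms, and assumed losses of 25% or 30% against 10%. The simulated bias of about 0.11 rests on a different mechanism with nearly equal losses, so the two do not confirm each other. It would be wrong to conclude that the plan is biased by 19% to 25% of its target effect. The direction is also unknown. The correction is worth making, but it does not invalidate the main analysis of a trial that its Trial design section calls exploratory.

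**What to change.** In the Statistical methods section, or in the analysis plan with the article's sentence corrected:

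- Keep the linear mixed model as the main analysis and state that it assumes MAR.
- Describe weighting, or multiple imputation with auxiliary variables, as MAR-based supporting analyses.
- Replace the MNAR sentence with a sensitivity analysis run whatever the attrition pattern: multiple imputation that respects classroom clustering, with imputed outcomes shifted by a prespecified range set separately by arm. A range of 0 to 0.5 SD is one example and is an assumption; the team should justify its own, since the simulated case needed 0.59 SD. Report the tipping point, that is, the shift at which the conclusion changes.
- Report by arm, as a separate source of possible bias, the students lost because parental consent was sought after allocation. They have no outcome data, and an analysis confined to consented students with some data would not cover them.

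The cost is a few lines of text and one extra sensitivity analysis. Conduct and data collection do not change, apart from keeping counts of non-consent by arm.

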##### Auditing

The Project Management team will meet monthly to discuss trial implementation or, upon necessity, if any potential difficulties arise. Additionally, the ethics committee is updated 6 months after the start of the trial or in the case that any changes to the trial protocol appear. The monitoring of unintended affects and inadvertent harm (e.g., unexpected, serious increases in symptomatology) will be undergone by team members who are also clinical psychologists and who will make referrals for appropriate interventions (i.e., clinical evaluation or psychotherapy), at which point the intervention will be discontinued immediately. Additionally, any such events will be appropriately and expeditiously reported to the ethics committee at the University of Bucharest.

The team responsible for recruitment and administrative tasks in the trial meets bi-weekly. The group consists of the principal investigator, project leader, and staff responsible for recruitment activities. The project leader, along with a research assistant, will monitor the trial, ensuring the eligibility of potential recruits, checking for the presence of informed consent, documentation of inclusion/exclusion criteria, and randomization for each participant. The project leader and research assistants will maintain constant communication with high schools and other relevant stakeholders.

### Ethics and dissemination

This study is approved by the ethics commission at the University of Bucharest. Since the recipients of the intervention are minors, careful consideration has been given to obtaining informed consent from parents or legal guardians, while also properly informing the students about the contents of the intervention that they are enrolled in. Participant data will be confidential and stored on secured servers. Additionally, since we also collect mental health data, special attention will be given to any increase in symptomatology or any participants presenting harm to themselves. If such situations arise, they will be handled by the clinical psychologists in the research team. Any subsequent changes to the protocol will be updated on ClinicalTrials.gov.

### Dissemination policy

We plan to publish the trial results in a peer-reviewed journal. Preliminary results will also be presented at international conferences, when appropriate. Additional plans are being made for the publication of the intervention manual. A summary of the results will also be made available for relevant stakeholders (i.e., high schools). Anonymized datasets will be made available upon reasonable request from the corresponding author.

## Discussion

The current trial aims to test the effectiveness of a mental health literacy intervention for high school students, aimed at improving academic performance, as well as increasing well-being and decreasing symptomatology. The intervention will be delivered via two different formats: (1) an educational one, which will be fully automated, and (2) a blended one which will additionally allow contact with facilitators, and it will be contrasted against a waitlist condition. Testing mental health literacy interventions is paramount, as not much is known about their effectiveness on outcomes such as academic performance and symptomatology. Furthermore, since the goal of mental health literacy interventions is to fill in the gaps that other mental health interventions cannot, in terms of their reach and cost-effectiveness, it also becomes highly relevant to test various modes of implementing such interventions, including fully automated ones. Additionally, testing the effectiveness of such interventions in varied cultural and socioeconomic contexts is timely, as this has been previously recognized as a limitation of the literature [19].

This endeavor, however, is not without its caveats. Firstly, contrasting active interventions against a waitlist control group can artificially inflate effect sizes. However, this approach is more ecological and cost-effective. If results will favor the SCHOLARS intervention, future studies should contrast it against active control conditions or psychological placebos. Secondly, there may be limited adherence to the intervention by the participants (i.e., dropouts). To this end, we aim to monitor and maintain close and constant contact with the enrolled schools, as to minimize drop-out and the risk of non-adherence by participants.

To conclude, the current study has the potential of advancing the field of mental health literacy interventions for adolescents. The success of such interventions might represent an important avenue for preventively addressing the development of mental health concerns and their associated consequences such as decreased academic performance.

### Trial status

Trial registration: https://clinicaltrials.gov/study/NCT06217744, Version 1, 22 January 2024. Recruitment for the trial has begun. Recruitment completion estimated date: November 2024.

## Data Availability

The datasets analyzed during the current study and statistical code used to analyze the data will be made available from the corresponding author upon reasonable request.
